The desire to quit smoking among Veterans is not lacking. Approximately 60-70% of all Veterans who smoke tobacco express interest in smoking cessation (Miller et al, 2001). A strong dose-response relationship between treatment intensity and cessation rates does exist (Fiore et., 2000). The most efficacious strategies found in VA smoking cessation clinics combine multiple formats of cognitive-behavioral interventions, including self-help materials, group therapy, and telephone counseling, resulting in a 23% abstinence rate (Fiore et al, 2000). These rates worsen in the context of comorbid psychiatric conditions, with specialty-based care smoking cessation efforts negatively affected by limited access and poor adherence (Jonk et al, 2005). Clinic attendance rates at specialty smoking cessation clinics are approximately 13-14% for all Veterans, and those with PTSD even less likely to follow up (McFall et al, 2010). Unfortunately, among Veterans with PTSD who do present to smoking cessation clinics, the efficacy of interventions is lower (McFall et al, 2010). This was demonstrated in the largest smoking cessation trial in Veterans with PTSD, with a biochemically verified (bio-verified; exhaled CO < 8 ppm or urine cotinine < 100ng/mL) cessation rate of only 4.5% at 12-months (McFall et al, 2010). These statistics underscore the urgency to consider alternative interventions for smoking cessation in this clinical population, including neuromodulaiton modalities such as rTMS.

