Overall Design: Fifty eligible participants will be randomized to one of 2 conditions: active-rTMS + CBT + NRT (n=25) or sham-rTMS + CBT + NRT (n=25). The full randomization sequence will be generated *a priori*. Participants will receive a baseline MRI scan, 5 daily neuronavigated active or sham rTMS treatments the week prior to their quit date, followed by a post-treatment MRI scan. In order to be able to use the fMRI results to inform placement of the TMS coils, there may be up to a two-week lag between the first MRI and the first TMS treatment session. All participants will receive 5 sessions of CBT for smoking cessation in which session 3 is designated as the quit date. All participants will also receive prescriptions of nicotine replacement in the form of 21 mg, 14 mg, and/or 7 mg patches and 2-4 mg nicotine gum or lozenges starting on the quit date and continuing for up to 90 days at individually tapered doses. All rTMS and MRI procedures will occur at Duke University Medical Center (DUMC). Participants will sign a Duke consent form and HIPAA authorization for those procedures.

We hypothesize that neuronavigated rTMS combined with CBT and NRT will be a safe, feasible, and effective method for smoking cessation in our study population. We anticipate being able to effectively recruit and retain eligible subjects in the study. Our primary feasibility endpoint will help determine successful completion of the study intervention and justification to continue this line of research. Recruitment will target enrolling 50 subjects, with a goal of 40 or more subjects completing at least 90% of all study procedures (>80% retention rate). We hypothesize that active- as compared to sham-rTMS will result in greater 7-day point prevalence abstinence rates (biochemically verified by exhaled carbon monoxide < 5 ppm) at end-of-treatment, and 3-month follow-up time points. We also hypothesize that active-rTMS will result in an increase in functional connectivity between the cortical rTMS target and the insula, therefore demonstrating target engagement. We also anticipate network-level differences in rsFC between active- vs sham-rTMS groups. We will also monitor levels of nicotine dependence, cravings, withdrawal, prolonged abstinence, psychiatric symptoms related to PTSD and depression, and alcohol use.

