Primary smoking outcome will be 7-day point prevalence abstinence based on subject self-report and confirmed using exhaled CO level at each follow-up assessment (i.e., end-of-treatment, 3-months post-quit date), with abstinence rates averaged over all assessments to take advantage of all available data and adjust for within-subjects clustering of data.115 This definition of abstinence is consistent with those previously used in studies of smoking cessation in Veterans.28 Non-abstinence will be defined as self-reported smoking (or other tobacco use) for 7 consecutive days or at least once a week for 2 consecutive weeks. Secondary outcomes will include daily number of cigarettes smoked, subjective levels of withdrawal, craving, and urges to smoke, 7-day point prevalence at 3-months post-quit date, as well as smoking relapse, defined as smoking 5 or more cigarettes per day for 3 consecutive days. We will evaluate 7-day point prevalence smoking abstinence by calculating a dichotomous outcome variable (abstinent or not abstinent) to determine the proportion of participants with bioverified abstinence at each assessment from quit date through 3 months follow-up. Due to the relatively small sample size, we will describe the rates of smoking abstinence by calculating the proportion of participants who are confirmed to be abstinent. We will calculate confidence intervals around the effect size to determine the level of variability expected in the subsequent full RCT.

Participants will be considered abstinent if they meet certain criteria, which we have used in prior work.97 For participants taking NRT at the time of follow-up, they will be considered abstinent if they self-report prolonged abstinence and provide a CO reading < 5 ppm. For those not taking NRT, abstinence will be based on: a) self-reported prolonged abstinence, b) absence of any biochemical samples indicating smoking (CO ≥ 5 ppm or cotinine ≥ 6 ng/mL), and c) presence of at least one biochemical sample indicating abstinence (CO < 5 ppm and/or cotinine < 6 ng/mL).

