Comparisons of continuous demographic and clinical data will be completed with linear regressions. Comparisons of dichotomous demographic and clinical data will use generalized linear models using a binomial distribution. Regarding 7-day point prevalence smoking abstinence outcomes at end-of-treatment, and 3-months; odds ratios and 95% confidence intervals will be computed from estimates obtained in generalized linear models. A longitudinal analysis using generalized linear models will also be conducted on abstinence across end-of-treatment, and 3-month time periods with predictors of treatment arm, time in months (standardized and centered), and the treatment arm-by-time interaction. All missing smoking data will be imputed as non-abstinent. All analyses will be conducted in R version 4.0.4.116

We will also complete analysis of neuroimaging data to determine target engagement. Specifically, we will focus on the correlation between changes on rsFC pre- and post-rTMS and change in the number of cigarettes smoked in the past 24 hours. We will also use a data-driven approach by employing group independent component analysis (ICA) to compare functional network connectivity (FNC) between active- and sham-rTMS groups including FC between rTMS target and right posterior insula.117

For the neuroimaging data, movement and scan artifacts will be detected using Artifact Detection Tools118 and included in the rsFC analyses as covariates of no interest. Group-level analyses will be conducted in SPM12. rsFC analyses will be confined to a bilateral insula regional of interest (ROI) mask defined from the Automated Anatomical Labeling (AAL) atlas with a significance threshold of p < .001 uncorrected, cluster extent > 10 voxels. Exploratory whole brain analyses will also be conducted with a significance threshold of p < .001 uncorrected, cluster extent > 50 voxels.

In the event that software required for analysis are not available through VINCI, deidentified data will be moved to Duke University Medical Center for analysis. Data will be emailed.

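### As named, the longitudinal abstinence model does not deliver the within-person clustering adjustment that the protocol promises for the same outcome

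*Protocol*

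**What the plan says.** All of this is in the protocol, Data Analysis and Statistical Considerations, Phase 2, unless stated otherwise.

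- **Primary smoking outcome.** Bioverified 7-day abstinence is assessed at end of treatment and at 3 months, with rates "averaged over all assessments to take advantage of all available data and adjust for within-subjects clustering of data". The method that does the adjusting is not named; there is only a citation number.
- **Single-visit effects.** For each of the two time points, "odds ratios and 95% confidence intervals will be computed from estimates obtained in generalized linear models".
- **Longitudinal model.** The plan adds a model for both time points together: "A longitudinal analysis using generalized linear models will also be conducted on abstinence across end-of-treatment, and 3-month time periods". Its listed terms are arm, centred time and their interaction. No random effect, working correlation, participant term or robust variance is listed. The section uses the same model term for baseline comparisons and single-visit odds ratios, where each person contributes one record.
- **Data going in.** There are 25 participants per arm (Phase 2 Research Design and Methods, Overall Design), and all 50 are analysed (Phase 2 Selection of Subjects). Missing smoking status counts as not abstinent, so every participant contributes two records.
- **Role.** The feasibility outcomes are recruitment and retention. For efficacy the aim is to estimate an effect size. No alpha, power or significance rule is given for abstinence.

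**The concern.** A person's two abstinence outcomes are likely to be positively correlated. Two of the protocol's own rules push the correlation up. Its abstinence criteria call for self-reported prolonged abstinence, which tends to make 3-month abstainers a subset of end-of-treatment abstainers. And anyone lost before end of treatment contributes two identical non-abstinent records.

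An ordinary generalized linear model would count 100 records as 100 independent people. The arm effect is a between-person comparison, so its standard error comes out too small. Arm-by-time is a within-person comparison, so its standard error comes out too large. At stake are an averaged effect that looks more precise than it is and an interaction test that would hardly ever show the effect changing over time.

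**Working it through.** **The plan's own figures.** The protocol states no error rate, power or correlation for abstinence, so there is nothing of that kind to reproduce. Its only sample-size arithmetic is consistent: 40 / (1 − 0.20) = 50.

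**Inputs.** From the protocol: 25 per arm, two visits, and complete records after the missing-data rule. Assumed: within-person correlation ρ, abstinence rates, and a two-sided 5% level (implied by the 95% intervals). The rates 28.4% and 11.7% come from the earlier civilian trial in Background and Significance and serve only to bracket the range.

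**Plausibility of ρ.** If every 3-month abstainer were also abstinent at end of treatment, with rates p1 and p2, then ρ = √[p2(1 − p1) / (p1(1 − p2))]. At 30% and 20% this is √(0.14/0.24) = 0.76. At 30% and 15% it is √(0.105/0.255) = 0.64. A range of 0.3 to 0.7 is therefore reasonable, but still an assumption.

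**Large-sample result.** With two balanced visits and centred time, the arm coefficient is the average of the two visit log odds ratios. If each has variance V:

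- Variance under independence: (V + V)/4 = V/2.
- True variance: (V + V + 2ρV)/4 = (V/2)(1 + ρ).
- Actual error for arm: 2[1 − Φ(1.96/√(1 + ρ))].
- Arm-by-time depends on the difference between the two log odds ratios, so 1 + ρ becomes 1 − ρ.

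For example, at ρ = 0.5: 1.96/1.225 = 1.600, which gives 11.0% for arm. For the interaction, 1.96/0.707 = 2.77, which gives 0.6%.

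| ρ | Correct width / GLM width, arm | Actual error, arm | Actual error, arm-by-time |
|---|---|---|---|
| 0.3 | 1.14 | 8.6% | 1.9% |
| 0.5 | 1.225 | 11.0% | 0.6% |
| 0.7 | 1.30 | 13.3% | 0.04% |

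**Simulation at the trial's size.** 200,000 trials per setting with no arm effect, 25 per arm, Wald test for arm. Data sets with no finite estimate were dropped.

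| Abstinence, end of treatment / 3 months | GLM, ρ = 0 | GLM, ρ = 0.3 | GLM, ρ = 0.5 | GLM, ρ = 0.7 | Cluster-robust, ρ = 0.3 to 0.7 |
|---|---|---|---|---|---|
| 30% / 30% | 5.0% | 8.4% | 10.7% | 13.2% | 4.3–4.8% |
| 28.4% / 20% | 4.5% | 7.9% | 10.0% | 12.2% | 3.5–4.2% |
| 20% / 15% | 3.4% | 6.3% | 8.4% | 10.5% | 2.5–3.3% |
| 11.7% / 11.7% | 1.7% | 3.6% | 5.1% | 6.8% | 1.1–1.8% |

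In the bottom row the Wald test is already conservative at ρ = 0 (1.7%) because counts are small, and that offsets the clustering error. About 14% to 16% of data sets in that row had no finite estimate for ρ of 0.3 to 0.7.

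**The case against.** The strongest reply is that the protocol never says visits are treated as independent. It states an intent to adjust for clustering, and 'longitudinal analysis using generalized linear models' can be loose shorthand that covers GEE or a mixed model. The correlation structure could be left to an analysis plan that is not shown. This stands in part: a reader might infer that the sponsor chose to ignore the correlation, and the text does not support that. But the protocol does fix the model family and the predictors, and it uses the same term for analyses with one record per person. Followed as written, the model does not do what the section promises.

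Three stronger readings are tempting and should be resisted.

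- **That the false-positive rate for arm doubles.** This is about right for ρ of 0.4 to 0.5 with abstinence of 20% or more. It is not right at ρ = 0.2 (7.4% in large samples) or near 12% abstinence. The protocol gives neither input, and it declares no test whose error rate could double.
- **That the intervals meant for planning the next trial are wrong.** The sentence about variability in that trial follows the abstinence proportions at each assessment. The longitudinal model comes later, as an additional analysis. The protocol does not say that planning will use its interval.
- **That the per-visit odds ratios share the defect.** They use one record per person, so clustering does not touch them. An arm without quitters would leave an odds ratio with no finite estimate, but that is a separate, contingent matter. The chance at one visit in a 25-person arm is (1 − 0.117)^25 = 4.5% at 11.7% abstinence. It is (1 − 0.045)^25 = 32% at 4.5%, but that rate is another trial's "cessation rate of only 4.5% at 12-months", not an expected rate at these visits. The proportions the protocol plans to report stay defined in any case.

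**Conclusion.** The point holds as an inconsistency with a numerical consequence. The section promises an adjustment for within-person clustering and then names a longitudinal model that has no means of making it. Fitted literally, the arm interval is too narrow by a factor of about √(1 + ρ), or 1.14 to 1.30 for ρ of 0.3 to 0.7. The arm-by-time test would reject in about 2% of null trials or fewer instead of 5%. Read as a test, arm would carry an error of about 6% to 13% at abstinence of 15% to 30%, and roughly 4% to 7% near 12%.

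These figures rest on assumed correlations and abstinence rates. The harm is over-narrow intervals from one additional efficacy model in a feasibility pilot. It should be fixed, but it does not threaten the trial's feasibility conclusions.

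**What to change.** In the Phase 2 analysis text, replace the generalized linear model for the longitudinal analysis with a binomial GEE: logit link, participant as cluster, exchangeable working correlation and small-sample-corrected sandwich standard errors. Keep arm, centred time and arm-by-time as predictors. Add that this analysis supplies the clustering adjustment described for the primary smoking outcome.

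GEE fits better here than a logistic model with a participant random intercept. It keeps the population-averaged odds ratio that matches abstinence rates averaged over visits, whereas a random intercept targets a participant-specific odds ratio and is weakly identified from two binary records per person.

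The cost is one sentence and a few lines of R, with no change to data collection. If each visit has one fixed nominal time, the point estimates are the same as from the GLM and only the standard errors change. The arm interval becomes about 14% to 30% wider for ρ of 0.3 to 0.7. In the simulations above, cluster-robust standard errors kept the error for arm below 5% in every setting. The per-visit odds ratios can stay as they are on this point.

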**Phase 2 Study Procedures**

Screening Visit: These study procedures are similar to Phase 1 of the project. Once considered eligible to participate in the study, participants will be randomized 1:1 to receive either active rTMS or sham rTMS. Participants will remain blinded to study condition throughout the study. [name] and [name] will also remain blinded to study condition.

Medical Screening: These study procedures are similar to Phase 1 of the project. However, in lieu of one screening session, we will divide the screen tasks between two visits. Diagnostic interviews will be completed at the first visit, and questionnaires and CO readings will be completed at the second.

Biochemical Verification of Abstinence: Participants will provide exhaled breath carbon monoxide (CO) levels at baseline, quit date, end-of-treatment, and at 3-month follow-up visit. We will use a standardized cutoff value of < 5 ppm. In addition, at the post-treatment and 3-month follow-up visit, urinary cotinine will also be collected for more comprehensive bioverification for those participants who are no longer using NRT. Urine samples collected will be sent to LabCorp for analysis.

DUMC Study Procedures: MRI procedures are identical to Phase 1 MRI procedures. MagVenture’s MagPro X100 will be used for rTMS procedures. rTMS parameters will be updated from Phase 1 to Phase 2 due to advances in the field and Phase 1 data. Phase 1 will be 5 daily rTMS sessions of 1 Hz 960 pulses for 16 minutes each. Phase 2 will be 5 days of rTMS treatments twice daily using patterned rTMS, intermittent theta burst stimulation (iTBS; 3-pulse 50-Hz bursts at 5-Hz for 2-s trains, with trains every 10 s) 1800 pulses at 90% rMT for 9 minutes each separated by at least 50 minutes. Active- or sham-rTMS will be determined by utilizing a subject-specific code recognized by the TMS device as active or sham, which then instructs staff as to which side of the TMS coil to use. The Magventure B65 A/P coil has identical sides, but the computer will know which side to use based on each participant code. A cue provocation procedure to induce nicotine cravings will be conducted prior to rTMS treatments using a video of smoking-related images as well as instructions for handling of a cigarette and lighter. Following the last rTMS session, a second fMRI scan (post-rTMS fMRI) will be conducted at least 1 hour and up to 24 hours later.

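### The significance rule for the insula connectivity analysis is uncorrected and counts extent in voxels, so its false-cluster rate is uncontrolled: about 4.5–12% or 0–3% in the hypothesised direction, depending on voxel size

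*Protocol*

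**What the plan says.** The rule stands in the Protocol, Data Analysis and Statistical Considerations, Phase 2. The purpose is stated first: "We will also complete analysis of neuroimaging data to determine target engagement". The search region follows: "rsFC analyses will be confined to a bilateral insula regional of interest (ROI) mask defined from the Automated Anatomical Labeling (AAL) atlas", and the sentence ends with the rule, "with a significance threshold of p < .001 uncorrected, cluster extent > 10 voxels". A second rule covers the rest of the brain: "Exploratory whole brain analyses will also be conducted with a significance threshold of p < .001 uncorrected, cluster extent > 50 voxels". The software is named: "Group-level analyses will be conducted in SPM12".

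The only image-processing step described is that "movement and scan artifacts will be detected using Artifact Detection Tools" and entered as covariates. Phase 2 Study Procedures says "MRI procedures are identical to Phase 1 MRI procedures", and the Phase 1 procedures give no voxel size or smoothing either. No family-wise or false-discovery-rate correction appears anywhere in the protocol, and the direction of the imaging test is not stated.

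Two other places give the rule its weight. The Phase 2 Overall Design hypothesises that active stimulation will increase connectivity between the stimulated cortical site and the insula, and treats that increase as evidence of target engagement. The Phase 2 outcome list then gives target engagement its own aim, defined on connectivity between the stimulation site and the right posterior insula.

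**The concern.** A threshold of p < .001 per voxel limits the error at one voxel. What will be reported is whether some cluster in the mask survives, and the mask holds thousands of voxels. A minimum cluster size reduces false clusters, but by an amount that depends on how large noise clusters are, measured in voxels. That depends on the resampled voxel size and the smoothness of the images. A fixed count such as "cluster extent > 10 voxels" is not tied to any chosen error rate, and it stands for a different tissue volume at each resolution.

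At stake is how a positive target-engagement result can be read. Such a result would help justify the later full trial, and a reader could not tell whether it came from a test run at well under 5% or at more than twice 5%. The issue is not a missing detail: the protocol states the rule and states that it is uncorrected. Giving voxel size and smoothing later would make the error rate calculable, but would not set it to any chosen level.

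**Working it through.** The protocol gives no false-cluster rate, so there is no figure to reproduce. The check asks what rate the written rule implies.

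**Inputs from the protocol.** Height threshold p < .001 uncorrected. Extent above 10 voxels, so 11 or more. Bilateral insula mask. 25 per arm, giving 25 + 25 − 2 = 48 degrees of freedom, or 38 with 40 completers.

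**Assumed, because not stated.** Mask volume 28–32 mL in total; voxels 2 or 3 mm isotropic; smoothness (FWHM) 6–12 mm; one-sided p within each direction.

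**Step 1: volume of the minimum cluster.** 11 × 2³ = 88 mm³; 11 × 3³ = 297 mm³; ratio 3.4.

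**Step 2: random field theory, worked example.** V = 28 mL, FWHM 8 mm, 48 degrees of freedom.
- Threshold: u = 3.269.
- Euler characteristic density: ρ₃ = (4 ln 2)^1.5 / (2π)² × [(47/48)u² − 1] × (1 + u²/48)^(−23.5) = 0.0098.
- Expected clusters: E[m] = (V/FWHM³) × ρ₃ = (28,000/512) × 0.0098 = 0.54.
- Mean cluster size: E[n] = 0.001 × (V/voxel volume) / E[m]. At 2 mm, 3.5/0.538 = 6.5 voxels. At 3 mm, 1.037/0.538 = 1.93 voxels.
- Chance that a cluster reaches 11 voxels: P = exp(−β × 11^(2/3)), with β = (Γ(5/2)/E[n])^(2/3). At 2 mm, β = 0.347 and P = 0.180. At 3 mm, β = 0.780 and P = 0.021.
- Chance of at least one false cluster, one direction: 1 − exp(−E[m] × P). At 2 mm, 1 − exp(−0.0967) = 9.2%. At 3 mm, 1 − exp(−0.0114) = 1.1%.
- Both directions: 1 − exp(−2 × E[m] × P) = 17.6% at 2 mm and 2.2% at 3 mm.

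**Step 3: simulation of null t-maps.** Two slabs of about 15 mL each, 48 degrees of freedom, 18-neighbour clusters, 600 runs per cell. Entries are the chance of at least one false cluster.

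| Voxel | Reading | 6 mm | 8 mm | 10 mm | 12 mm |
|---|---|---|---|---|---|
| 2 mm | one direction | 4.5% | 9.2% | 9.7% | 9.2% |
| 2 mm | both signs | 8.8% | 17.7% | 18.7% | 17.0% |
| 3 mm | one direction | 0% | 0.9% | 2.0% | 3.1% |
| 3 mm | both signs | 0% | 1.8% | 4.0% | 6.0% |

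Thinner slabs of about 16 mL each, at 2 mm with FWHM 8, 10 and 12 mm (500 runs per cell), give 10.2, 11.9 and 10.5% in one direction and 19.6, 21.6 and 20.0% for both signs.

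**Step 4: a different geometry.** Two 14 mL ellipsoids, 38 degrees of freedom, both signs. At 2 mm with FWHM 6, 8 and 10 mm: 46/550 = 8.4%, 86/550 = 15.6% and 45/200 = 22.5%. At 3 mm with FWHM 8 and 10 mm: 4/650 = 0.6% and 12/400 = 3.0%. The 22.5% has a standard error of √(0.225 × 0.775/200) = 3 percentage points.

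The three approaches agree closely enough that shape and degrees of freedom do not drive the result. Voxel size does, followed by whether one or both signs are read.

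**The case against.** **The percentages belong to assumed settings, not to the protocol.** This is correct. Voxel size, smoothness, mask volume and sidedness are all assumed. With 3 mm voxels the rule is stricter than 5% in the hypothesised direction. A reader might infer that the rule inflates error. The documents do not support that; they support only that the rate is not controlled and can fall on either side of 5%.

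**The highest figures ignore the stated direction.** This also stands. The protocol predicts an increase, and about 22% needs 2 mm voxels, smoothness near 10 mm and both signs read. In the predicted direction the most found is about 12%.

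**Voxel size and smoothing are details for a statistical analysis plan.** True of those parameters, and one of the documents not at hand may fix them before any scan is seen. A reader might infer that the same data could be made significant by processing choices made after seeing the scans. Nothing in the protocol says or implies this. The objection does not rescue the threshold, which the protocol itself fixes as uncorrected.

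**Target engagement is defined on one pair of regions, and the text also relies on a correlation with smoking change and on a component analysis.** Fair as a limit: the protocol never says that any surviving cluster anywhere in either insula will count as engagement. Still, the rule governs the connectivity analyses in the mask, the section gives their purpose as determining engagement, and no other significance rule is stated for them.

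**The whole-brain analysis is declared exploratory.** Accepted, so it is only a secondary matter here. Its rate is equally open. In simulation (60–80 runs per cell, assumed brain of 1.46 L) with 2 mm voxels and FWHM 8, 10 and 12 mm, it is 23, 45 and 60% in one direction and 44, 70 and 81% for both signs. With 3 mm voxels it is 0% at 8 mm and 5% (10% both signs) at 12 mm. A reader might take 70% as an upper limit; it is not one.

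**Conclusion.** The concern holds for the insula rule. As written, it does not control the chance of at least one false cluster in the bilateral mask, and that chance moves with voxel size and smoothness. Under the assumed mask and smoothness ranges, the hypothesised-direction rate is from just under 5% to about 2.4 times 5% (11.9/5) with 2 mm voxels, and below 5% with 3 mm voxels. Reading both signs roughly doubles each figure. A smaller search region, such as the right posterior insula alone, would lower the rates but leave them equally uncontrolled.

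The consequence is confined to the target-engagement aim. Recruitment and retention, the primary feasibility outcome, are untouched, and the threshold is openly labelled as uncorrected. The change is worth making because the aim carries its own hypothesis and a better-defined rule costs almost nothing.

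**What to change.** Replace the insula rule with one that fixes the error rate:
- Form clusters at voxel-wise p < .001 and declare significance at family-wise-error-corrected p < .05, small-volume corrected within the prespecified insula region. SPM12, already named, provides this.
- State which insula region the correction covers, since the outcome names the right posterior part and the analysis a bilateral mask. State the contrast and the direction tested.
- Show uncorrected maps as descriptive output only.

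As a secondary point, label the whole-brain maps descriptive, or apply cluster-level family-wise-error-corrected p < .05 to them.

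The cost is a change to two sentences, in the protocol or the statistical analysis plan, with no new data or visits. The downside is that fewer clusters may be declared at fine voxel sizes. At coarse voxel sizes the corrected rule guards against being needlessly strict.
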